### Control arm – current practice

Conventional cytology (or LBC in our site) is the screening tool used in this arm. Triage algorithm is based on Recommendations of the Polish Gynaecological Society [18]. The smears are interpreted according to a modification of the TBS. Women with abnormal Pap smear results are supposed to be triaged within the Programme with 1) repeated Pap smear for atypical squamous cells of undetermined significance (ASC-US), low grade squamous intraepithelial lesion (LSIL) or 2) colposcopy (with or without targeted biopsy) for repeated ASC-US and LSIL, or first observation of atypical squamous cells – cannot exclude high grade squamous intraepithelial lesion (ASC-H), high grade squamous intraepithelial lesion (HSIL), atypical glandular cells (AGC), squamous cell carcinoma (SCC), adenocarcinoma in situ (AIC). If the screening cytology result is negative, rescreening is scheduled after 3 years. Medical records of procedures performed in the OCCSP are stored in the central electronic database (SIMP). hrHPV testing recommended for triage of ASC-US and LSIL [8] is not available in the Programme but can be performed within NHF-reimbursed gynaecological services. The scheme of the algorithm is presented in Fig. 2.

**Fig. 2 Fig2:**
[figure not shown]
Algorithm of control arm. ASC-US—Atypical Squamous Cells of Undetermined Significance. CC – cervical cancer. hrHPV test—high risk Human Papillomavirus test. LBC—Liquid-Based Cytology. LSIL—Low-Grade Squamous Intraepithelial Lesion. NILM—No Intraepithelial Lesion or Malignancy

Cervical cytology samples taken by the midwives or gynaecologists are collected using a cervical brush and placed on a glass slide for conventional cytology or in SurePath medium (BD Totalys Slide Prep, Becton Dickinson TriPath) for LBC [19].

Currently, facilities participating in the OCCSP are mandated to monitor patients' outcomes and actively invite women with abnormal results from the initial stage examination for further in-depth diagnostics. However, due to organisational challenges and a lack of effective oversight, monitoring is not working very well.

### New screening test and triage algorithm – hrHPV test arm

Clinically certified hrHPV tests in the experimental arm must fulfil Meijers criteria [20] and must have been validated in Valgent platform [21]. All used assays allow the detection of two HPV genotypes (16, 18) and the identification of twelve additional genotypes (31, 33, 35, 39, 45, 51, 52, 56, 58, 59, 66 and 68). hrHPV testing is performed with the Cobas 4800 HPV Test (Roche Molecular System, Pleasanton, CF, USA), INNO-LiPA HPV Genotyping Extra II assay (INNO-LiPA; Fujirebio Europe, Ghent, Belgium), Onclarity HPV Assay (BD Diagnostics, Sparks, MD, USA), Harmonia HPV (Liferiver, Shanghai, China), AmpFire Multiplex HPV Assay (Atila BioSystems, Mountain View, CA) on the BD SurePath which complies with the International Guidelines for HPV Test Requirements for Cervical Screening. Results are reported as HPV negative, HPV positive (HPV16, HPV18 and/ or other HPV types) or invalid. Cervical samples are taken by a gynaecologist or a certified midwife in OCCSP in Poland.

Women with HPV-negative results are released for the next round with a five-year interval. If hrHPV is detected, a reflex LBC on the same sample is conducted. HPV-positive women with abnormal cytology (ASC-US or worse) are directly referred for colposcopy with mandatory biopsy (punch biopsy, or Large loop excision of the transformation zone (LLETZ), with or without endocervical curettage upon decision by the colposcopist). The referral is automatically issued by the SIMP for ≥ ASC-US. Patients are informed by medical staff about the colposcopy reference centres in the OCCSP. If histological results by any means are obtained outside the OCCSP the site coordinators are responsible for full acquisition and registration of histological outcomes.

hrHPV-positive, reflex LBC-negative women are invited to LBC retesting after 6 months. After six months women with ASC-US or higher abnormality are referred for colposcopy with necessary biopsy. In hrHPV-positive and two subsequent NILM results, CINtec® PLUS Cytology tests and the QIASURE methylation tests are performed. If the result of at least one of them is positive, the patient is referred for colposcopy with biopsy. If both tests are negative, the woman returns in a shortened screening interval in 3 years. The scheme of the hrHPV arm is presented in Fig. 3.

**Fig. 3 Fig3:**
[figure not shown]
Algorithm of hrHPV arm. ASC-US—Atypical Squamous Cells of Undetermined Significance. CC – cervical cancer. hrHPV test—high risk Human Papillomavirus test. LBC—Liquid-Based Cytology. LSIL—Low-Grade Squamous Intraepithelial Lesion. NILM—No Intraepithelial Lesion or Malignancy

Patients had planned visits according to the study algorithm:

Visit 1: screening test (*test hrHPV* ± *LBC).*Visit 2': colposcopy with biopsy (*women with hrHPV (* +*),* ≥ *ASC-US in screening test*),Visit 2’’(after 6 month): LBC *(women with hrHPV (* +*) and NILM in screening tes*t).Visit 3’: colposcopy with biopsy (*women with hrHPV (* +*), NILM and* ≥ *ASC-US in LBC after 6 months*).Visit 3’’: colposcopy with biopsy (*women with HPV (* +*), double and CINtec PLUS Cytology (* +*) and/or QIASURE Metylathion test (* +*)*).

All reports of visits and results are available in the SIMP.

The purified DNA material after HPV test is banked and stored at − 80 °C. CINtec® PLUS Cytology (p16/Ki67 cytology dual staining) and QIASURE methylation test are performed on the residual SurePath cell-pellet.

## Discussion

Population-based cytological screening has the potential to reduce CC incidence and mortality through identification and treatment of precancerous lesions. However cytology is not a perfect screening test due to its limited sensitivity, and subsequent risk of interval cancers, in particular of adenocarcinoma.. A pilot audit of false negative cytological results was conducted in Poland and revealed a considerable burden of false negative Pap smears which resulted in interval cancers [6].

Identification of hrHPV as the aetiological factor of CC enabled elaboration of very sensitive molecular technologies which may replace cytology as a primary screening test and potentially provide better outcomes of screening. A number of randomised controlled trials comparing hrHPV testing to cytology, specifically the detection of high grade CIN (CIN 2 + and CIN 3 +), have been executed [22–25]. Based on meta-analyses, hrHPV primary screening has higher sensitivity than cytology primary screening in detecting precancerous cervical lesions (CIN2 + and CIN3 +), so it gives increased protection against development of CC [2, 26]. Due to the higher cross-sectional and longitudinal sensitivity, longer intervals and decreasing costs of hrHPV testing on a large scale, molecular screening has been proven to more effective and cost-effective than cytology and should be considered for implementation in screening programmes [8, 27]. The disadvantage of hrHPV testing is that it is less specific than cytology and therefore requires appropriate triage [28]. So according to the European guidelines for quality assurance in CC screening, before implementation of hrHPV primary testing to routine population-based CC screening programme, it is recommended to conduct pilot evaluation to ensure that an appropriate balance between harms and benefits may be achieved [2]. Recently the Netherlands, Turkey, England and Australia have implemented primary hrHPV-based screening programmes. Sweden, Finland, Germany and Italy have regional hrHPV primary testing or are at the roll-out phase. Some other countries are in the process of transition from cytology-based to hrHPV-based screening [29]. Management of hrHPV positive women remains a challenge for clinicians since no optimal, “gold-standard triage protocol” has been developed. Many triage strategies are being tested, however amongst them, two most common ones can be distinguished. First is based on performing reflex LBC after detection of any hrHPV type (Netherlands) and second uses HPV 16/18 genotyping to identify women with the highest risk for high-grade precancerous lesions and the need for direct referral for colposcopy (Australia, Italy) [22, 30].

The Netherlands was the first country to switch to hrHPV screening (January 2017). The algorithm of the HIPPO project is largely based on the Dutch CC screening programme since at the time of the development of our protocol, the Dutch programme was the only standardised hrHPV-based algorithm and used routinely in everyday clinical screening practice. In order to obtain final histological endpoints and to increase the sensitivity of mere colposcopy (without biopsy) commonly performed in Poland, we have implemented mandatory collection of at least one tissue sample (upon decision of the colposcopist) during colposcopy in the hrHPV arm. We have also decided to shorten the interval to 3 years for hrHPV-positive, twice LBC-negative women since in those women we consider the risk of CIN3 + development higher than in hrHPV-negative individuals.

In 2018 (after the first 18 months), the Dutch programme analysed referral for colposcopy and detection rate of CIN in women in screening based on hrHPV and cytology (tests performed between January 2015 to March 2016, before implementation of new screening programme). The result was, as expected, higher CIN2 + detection rate in the new hrHPV-based screening than in the cytology-based programme before [31]. In addition, more low-grade lesions were found in the newer compared to the older programme. Therefore, molecular screening may result in an increased number of unnecessary colposcopies, treatments, and adverse effects, particularly in younger women [31]. Among women aged ≥ 35 years, HPV primary screening entails only a limited increase in overdiagnosis of non-progressive lesions compared with cytology primary screening. The ATHENA trial supports the triage based on genotyping and direct referral of HPV16/18 positive women for colposcopy since they have the highest risk of CIN3 + diagnosis [23]. Australian [32] and Italian [29] Cervical Screening Programme algorithms are also based on HPV testing and genotyping for initial triage. However these programmes were initiated after the Dutch HPV-based screening programme on which we based the HIPPO protocol. American Society for Colposcopy and Cervical Pathology (ASCCP) decided to assist healthcare professionals with management of women attending CC screening and developed an evidence-based management guideline-mobile application stratifying risk of CIN3 + based on several pieces of data. However it was also launched when the work on the HIPPO protocol was well advanced and it was not included in our triage strategy.

Recently new data emerged [33] and FDA approval [34] was granted to novel biomarkers for use in triage of hrHPV-positive women. The CINtec® PLUS Cytology test is the first Food and Drug Administration (FDA) approved test to triage women with positive results of hrHPV test. The QIASURE methylation test (QIAGEN) has gained attention from researchers and data on its potential usefulness in triage of hrHPV women [33, 35]. Therefore in 2020 we amended the protocol of the HIPPO project and decided to compare the performance of these two tests in identification of high-grade cervical lesions in hrHPV positive and twice LBC negative women. Women who are tested positive on either of these tests are referred to colposcopy with mandatory histological verification. Women who test negative on both tests will be rescreened with hrHPV test in three years. The project will enable verification of the diagnostic yield of these two tests in detection of histologically confirmed CIN2 + in women with hrHPV-positive results and two 6-months apart NILM Pap results prospectively which has not been yet investigated. Data gathered in the HIPPO project will be subject to extensive analysis. Results will be important for clinical decision-making and setting-up appropriate algorithms. Data will be submitted to the Polish Health Technology and Tariff Agency for cost-effectiveness evaluation to guide decision-makers on the potential switch to molecular-based testing. Altogether this should facilitate the identification of a robust CC screening strategy in a reimbursed programme based on local evidence. Hopefully the introduction of HPV-based screening will accelerate the decreasing trends in CC burden in the country.

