**Fig. 1 Fig1:**
[figure not shown]
The flowchart of women enrolled in the HIPPO trial. ASC-US—Atypical Squamous Cells of Undetermined Significance. CC – cervical cancer. hrHPV test—high risk Human Papillomavirus test. LBC—Liquid-Based Cytology. LSIL—Low-Grade Squamous Intraepithelial Lesion. NILM—No Intraepithelial Lesion or Malignancy

Inclusion criteria to the project are: i) age 30–59 and ii) without screening Pap test within the preceding three years (or one year for women with risk factors: HR HPV infection/HIV infection/use of immunosuppressive drugs entitled to annual screening based on information from the SIMP) in the OCCSP. Exclusion criteria for study are: the Pap test taken within the preceding three years in the OCCSP and illegibility for screening according to SIMP (previous treatment, hysterectomy etc.).

Women attending the selected screening sites are informed on the project by trained site personnel using pilot-tested information brochures with detailed information about the study, objectives of the study, duration, procedures, potential risks and benefits. By the decision of the Ministry of Health in Poland signing an informed consent is required from women to participate in the study. Women who accept participation are randomised by the SIMP to the competing screening tests and strategies. The sample takers and researchers involved in data collection and monitoring are aware of the arm to which each participant is assigned. The patients are informed about which arm they are also assigned to and they cannot change their arm. A questionnaire with screening history (participation in opportunistic screening, treatment of cervical lesions, HPV vaccination status etc.) are collected from participating women.

The primary endpoint is the detection rate (DR) of histologically confirmed CIN2 or higher in each screening arm and detection rate ratio (DRR) of CIN2 + in HPV test *vs* cytology arm in intention-to-treat (ITT) analysis. Secondary endpoints include detection rate ratio of CIN1 + , CIN3 + (including adenocarcinoma in situ) and invasive CC in both ITT and per-protocol (PP) analysis, restricted to women who adhered to the foreseen follow-up.

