Site coordinators are contracted to monitor patients with abnormal screening test results in both arms. They are responsible for full acquisition and registration of histological outcomes. Coordinators regularly provide detailed reports to the main centre—Cancer Prevention Centre.

Additionally, biobanking of cytological samples taken from patients participating in the HIPPO project is performed in the Maria Sklodowska-Curie National Research Institute of Oncology for the purpose of potential future retrospective analyses if new CC screening or triage technologies emerge.

The study groups will be compared using two-sided tests: chi square test or analysis of variance (ANOVA, Kruskall-Wallis test). A chi-square test will be used to compare the characteristics of patients in different groups. The Kruskal–Wallis test will be used to compare differences in variables between two groups. If variations exist, a logistic regression analysis will be performed to permit control of potential confounding factors. The statistical significance in the experimental group compared with control will be analysed by ANOVA. Results will be considered statistically significant at the 0.05 significance level. The groups will be characterised by descriptive statistics: cardinality and percentage for discrete variables, mean and standard deviation for continuous variables with normal distribution, median and interquartile range for continuous variables with different distribution. The distribution of variables will be assessed among the groups. If variations exist, a logistic regression analysis will be performed to permit control of potential confounding factors. All analyses will be carried out with Stata 14.1 [14].

The study hypothesis assumes that the detection rate of histologically confirmed CIN2 + is significantly higher when HPV HR tests are used for screening in comparison to current standard of cytology (conventional or LBC).

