## Strengths and limitations of the study

This is the first randomised controlled trial to evaluate and compare performance of an investigational screening strategy: HPV molecular testing with cytology (conventional cytology/LBC) in everyday clinical practice in the OCCSP in Poland.

This trial will clarify whether screening using HPV testing detects more CIN2 + than routine screening based on cytology.

A major strength of this study is the large group of included patients in both screening arms.

The limitation may be selected population. Women can have current screening test results in private care.

Expectation bias may observe in the study. Medical staff has information which patients are participated in the project (and cytology/hrHPV arm).

The assumption that all ASC-H or worse will lead to a diagnosis of CIN2 + upon final histological examination is not accurate. This rate can be lower, but LSIL and ASC-US results may also manifest as CIN 2 + [36–38].

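### Biopsy is mandatory at colposcopy only in the hrHPV arm, so the primary CIN2+ detection-rate ratio cannot be credited to the screening test alone and is expected to lean towards HPV by an unknown amount

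*Protocol article*

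**What the plan says.** The primary endpoint (protocol article, Methods, after Figure 1) is the detection rate of histologically confirmed CIN2+ in each arm and the HPV-to-cytology DRR, by intention to treat.

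Biopsy at colposcopy differs by arm:

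- **hrHPV arm.** Women with abnormal reflex cytology "are directly referred for colposcopy with mandatory biopsy" (section on the hrHPV test arm). The Discussion says "we have implemented mandatory collection of at least one tissue sample (upon decision of the colposcopist) during colposcopy in the hrHPV arm", and women positive on a triage biomarker are "referred to colposcopy with mandatory histological verification".
- **Cytology arm.** The section on the control arm specifies "colposcopy (with or without targeted biopsy) for repeated ASC-US and LSIL". The same clause covers first-time ASC-H, HSIL and the other high-grade or glandular results, so biopsy is optional for every route to colposcopy.

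The Discussion gives the reasons for the hrHPV-arm rule: to secure histological endpoints and "to increase the sensitivity of mere colposcopy (without biopsy) commonly performed in Poland".

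On interpretation, the hypothesis in Methods concerns the use of HPV tests for screening. The sample-size paragraph takes its ratio of 1.5 from the relative sensitivity of the HPV test against cytology. The strengths section says "This trial will clarify whether screening using HPV testing detects more CIN2 + than routine screening based on cytology". The limitations listed there are the selected population, expectation bias and the ASC-H assumption. Unequal histological verification is not among them.

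**The concern.** The outcome is looked for harder in the arm that the hypothesis favours. Suppose two women, one in each arm, have the same CIN2+ lesion and both reach colposcopy. The hrHPV-arm woman must have tissue taken and can become a case. The control-arm woman becomes a case only if the colposcopist chooses to biopsy, or if tissue is obtained on another occasion.

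The authors' own rationale supplies the direction, since they introduced the rule because colposcopy without biopsy is less sensitive. A larger sample does not reduce this bias. Randomisation does not remove it either, because it arises after allocation.

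What is at stake is attribution. The results are meant to inform a decision on moving the national programme to HPV-based screening. A gain that came from biopsying more thoroughly could be read as a gain from the HPV test, although a biopsy rule is separable from the screening test.

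**Working it through.** **Inputs from the article (Methods).** Control-arm CIN2+ rate 0.5%; hrHPV-arm rate 0.75%; ratio about 1.5; alpha 5%, two-sided tests; power 80%; 1:1 allocation; about 16,500 per arm; predicted control-arm colposcopy referral 1.3%.

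**Input not in the article.** v, the share of control-arm CIN2+ reaching colposcopy that is histologically confirmed, relative to the hrHPV arm. It is assumed and shown as a range.

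**Step 1: the plan's own sample size.**
n = [1.960·√(2·p̄(1−p̄)) + 0.842·√(p₁(1−p₁) + p₂(1−p₂))]² / (p₂−p₁)², with p₁ = 0.005, p₂ = 0.0075, p̄ = 0.00625.
This gives 15,599 per arm, or 16,389 with the continuity correction, which agrees with about 16,500. The calculation is sound, but its 1.5 is a test-sensitivity ratio and contains no verification effect.

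**Step 2: expected DRR with no test difference.** Let both arms bring the same true CIN2+ rate p to colposcopy. The hrHPV arm records p and the cytology arm records v·p, so the expected DRR is p/(v·p) = 1/v.

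**Step 3: chance of a significant result.** With p = 0.005, n = 16,500 and a pooled two-proportion z-test, P(significant for HPV) = Φ{[(p − v·p) − 1.960·SE₀]/SE₁}.
For v = 0.8 the rates are 0.0050 and 0.0040, the difference is 0.0010, and SE₀ and SE₁ are both about 0.000737. Then (0.0010 − 0.001444)/0.000737 = −0.60, and Φ = 0.273.

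| Control-arm shortfall (1−v) | Recorded rates, HPV vs cytology | Expected DRR | Two-sided rejection (nominal 5%) |
|---|---|---|---|
| 0% | 0.50% vs 0.50% | 1.00 | 5% |
| 10% | 0.50% vs 0.45% | 1.11 | about 10% |
| 20% | 0.50% vs 0.40% | 1.25 | about 27% |
| 30% | 0.50% vs 0.35% | 1.43 | about 55% |

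Nearly all of these rejections favour HPV. At a 10% shortfall, 9.7 of the 10.1 percentage points do.

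**Step 4: what the shortfalls mean in women.** 0.5% of 16,500 is 82.5 CIN2+ cases, and 1.3% of 16,500 is 214.5 referrals. A 20% shortfall is 16.5 unconfirmed lesions, or 16.5/214.5 = 7.7% of control-arm referrals. A 30% shortfall is 24.75 lesions, or 11.5% of referrals.

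**Step 5: reading an observed ratio.** If the observed DRR were 1.5, the ratio under equal verification would be 1.5·v: 1.35, 1.20 or 1.05 for v = 0.9, 0.8 or 0.7.

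The table treats hrHPV-arm confirmation as complete. Only the ratio of the two confirmation shares affects the DRR.

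**The case against.** **The trial compares strategies.** The Aim sets an investigational screening strategy against current practice, and Methods describes randomisation to competing tests and strategies. The hrHPV arm also bundles reflex cytology, repeat cytology at six months and two biomarkers, so the DRR never isolated the test. This largely stands, and the fix adopts it. But the article is not consistent: the assumed 1.5 is a relative test sensitivity, and the hypothesis and strengths wording can be read as crediting the test.

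**Histology is pursued in both arms.** "Site coordinators are contracted to monitor patients with abnormal screening test results in both arms", and those coordinators are responsible for registering histological outcomes. Final diagnosis is planned to run to December 2023, so some lesions missed at one colposcopy may be confirmed later. This reduces the loss but does not remove it, because coordinators can register only tissue that was taken.

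**The size is assumed.** This stands. A modest bias is quite possible. For illustration, suppose half of control-arm referrals are un-biopsied and 10% of those women have CIN2+. The shortfall is then 0.5·0.10·1.3/0.5 = 13%, and the DRR 1/0.87 = 1.15. With 30% un-biopsied the shortfall is about 8%.

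**Sensitivity analyses belong in an analysis plan.** Agreed: that document is not shown, and their absence from the article is not the complaint. The complaint is a stated asymmetry in endpoint ascertainment, alongside wording that attributes the result to the test and a limitations list that omits the asymmetry.

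**Conclusion.** The point holds as a matter of attribution. Histological verification is unequal by design, it acts directly on the primary endpoint, its expected direction favours HPV, and the article does not acknowledge it. The rejection rates of about 10%, 27% and 55% are scenarios. They assume identical tests, a true rate of 0.5%, 16,500 women per arm and shortfalls of 10%, 20% and 30%.

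Three stronger readings are tempting, and the article does not support them:

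- **That the hypothesised effect could simply be an artefact.** A one-third shortfall would indeed give 1/(2/3) = 1.5 with no test difference. It would require un-biopsied CIN2+ in 0.333·0.5/1.3 = 12.8% of all control-arm referrals, and nothing in the article indicates a figure that high.
- **That the comparison is invalid.** As a contrast of two complete strategies, each with its own biopsy policy, the DRR is interpretable. It is the step from strategy to test that fails.
- **That the national decision hangs on this ratio alone.** The data also go to a cost-effectiveness evaluation, and referral rate, colposcopy compliance and predictive value of referral are further outcomes.

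**What to change.** No biopsy rule needs to change, and no view is taken on which rule is clinically right.

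1. **Wording.** In the endpoint and hypothesis paragraphs of Methods and in the strengths section, state that the primary DRR compares whole screening strategies, including their different biopsy policies at colposcopy. Add unequal histological verification to the limitations, with its expected direction.
2. **Reporting.** By arm and referral cytology, give the proportion of colposcopies with histology and the number of CIN2+ per biopsy. Coordinators would need to record, for each colposcopy, whether tissue was taken, including those done outside the programme.
3. **A bounding sensitivity DRR.** For referral cytology k in the control arm, let u_k be the un-biopsied colposcopies and q_k the CIN2+ proportion among biopsied women. Replace the control-arm count x_C by x_C + λ·Σ(u_k·q_k) and let λ run from 0 to 1. Label λ = 1 as a bound: if colposcopists biopsy the more suspicious cases, un-biopsied women carry less risk than q_k. Attribute the gain to the HPV test itself only so far as it is robust over this range.

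The bound should not become a formal condition for declaring superiority, because its upper end is deliberately extreme. Nor should hrHPV-arm cases be recounted under a visible-lesion rule, because the control-arm section states no such criterion.

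The cost is some wording, one table, one sensitivity analysis and a more cautious conclusion.
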